## Methods

### Aims

The planned study focusses on optimal content (criteria-based programme), general setting of preoperative training and supervision (one-on-one guidance or self-administered training). With this randomised-controlled trial, our objective is to compare the effects of a guided, structured and criteria-based preoperative rehabilitation programme, which can be adapted to the individual performance level, to a non-guided and self-administered home-based training programme on functional and self-report outcomes and secondary issues (other knee function, daily living and return to sport). The KOOS sum score (Knee Injury and Osteoarthritis Outcome Score) is the primary outcome and assesses the self-perceived knee function [15, 16]. We hypothesise that the guided prehabilitation programme will be more effective than self-administered home training relating to its effect on the baseline to pre-reconstruction change score of the KOOS sum score.

We will investigate the effects of pre-operative training (guided vs. unguided) at different time points (pre-op, 30/60/90/180 days post-op). We expect that the guided prehabilitation programme will have a particularly positive short-term effect and that the difference between the two groups will decrease over the progress of rehabilitation.

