## Outcomes

Functional parameters as well as self-reported knee function will be collected in both groups at seven defined measurement time points (anamnesis in the hospital, 1–7 days before ACL reconstruction, on the day of surgery, and 30, 60, 90, and 180 days postoperative) (Fig. 4). The primary time point is 1–7 days before ACL reconstruction.

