### Sample size determination

The sample size calculation is based on the sum score of the KOOS (primary outcome parameter). The difference in the KOOS score of the comparator and intervention group at the measurement pre-reconstruction will be compared. The minimal clinically important change (MIC) for the KOOS score is reported to be a change of 8–10 with respect to the subscale score in patients with knee injuries [36]. For performing a sample size calculation, usually, a standard deviation of SD = 15 is used for the KOOS score [16]. On this basis, an effect size of *d* = 0.533 was calculated using G*Power [37]. With a power of 80% and a one-sided alpha error level of 2.5%, data must be collected from *n* = 114 participants (equal number of participants in comparator and intervention group of *n* = 57 participants).

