### Statistical analysis

The two-sided alpha-error threshold will be set at 5% for all inference statistical analyses: all p-values below this value will be considered as statistically significant. All statistical analyses will be performed using R statistic (R version 4.2.3 or newer). We will follow the CHAMP statement when designing and reporting the statistical analysis [38].

Baseline data will be displayed as means and standard deviations, while the main outcome data will be displayed as means and 95% confidence intervals.

Following plausibility control (physiological range check, formal outlier analysis), the main analyses will be conducted based on the intention-to-treat principle. For that purpose, a multiple imputation, assuming missing completely at random and using chained equations in a fully conditional specification with 40 iterations to produce asymptotically unbiased estimations of the data, will be performed.

The group affiliation of the participants (intervention group: prehabilitation, comparator group: home training) will be defined as a between-subject factor. The main analyses are calculated as linear mixed models for repeated measurements. Main inference statistical analyses will be performed using each outcome’s change scores from baseline to each follow-up as the dependent variable. These analyses will be performed confirmatory. The time effects (repeated measures) will be modelled as random effects (and factors), and the other independent variables (group) and covariates (potential confounders and effect modifiers) as fixed effects. In the same model, the influence on the treatment effect by clinically important confounders and effect modifiers age, gender, and activity level will be calculated.

Patients, who do not have surgery, will not be included. If patients will decide after inclusion that they do not want surgery after all, the last testing will be done before the originally scheduled surgery date (intention-to-treat).

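### The protocol makes every outcome's change at every follow-up confirmatory at an unadjusted 5%, although the trial is defined and sized for one primary comparison

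*Protocol article*

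**What the plan says.** The Statistical analysis section of the protocol article sets the level and the decision rule once, for everything: "The two-sided alpha-error threshold will be set at 5% for all inference statistical analyses", and "all p-values below this value will be considered as statistically significant". It then defines the main inferential analyses as taking each outcome's "change scores from baseline to each follow-up as the dependent variable". The next sentence is "These analyses will be performed confirmatory". Read in order, that sentence refers to all outcomes and all follow-ups. The section gives no order of testing and does not mark one analysis as primary.

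Other sections are narrower. Aims states one directional hypothesis, that the guided programme is superior in "its effect on the baseline to pre-reconstruction change score of the KOOS sum score". Outcomes adds: "The primary time point is 1–7 days before ACL reconstruction". The section on the primary outcome names only the KOOS. Sample size determination rests on the KOOS group difference at the pre-reconstruction measurement. The functional and return-to-sport measures stand under the heading Secondary outcomes.

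**The concern.** A confirmatory analysis is one whose significant result may be reported as an established effect, which normally presumes control of error over all the claims that may be made. Here the status is given to every outcome at every follow-up, each at 5%, in a trial that elsewhere has one primary outcome at one time point. The two positions do not fit together.

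What is at stake is the reporting. If KOOS change at the pre-surgery visit shows no difference, but range of motion at 30 days or KOOS at 180 days has p < 0.05, the text as written supports presenting that result as prespecified and confirmed. Aims itself expects the group difference to shrink during rehabilitation, yet the 180-day comparisons get the same status as the pre-surgery one.

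**Working it through.** **1. The plan's own figure.** Sample size determination gives a KOOS change of 8–10 points, SD 15, d = 0.533, one-sided 2.5% and 80% power. The lower end gives d = 8/15 = 0.533. For a two-sample t test with n per arm, the degrees of freedom are 2n − 2 and the noncentrality is d·√(n/2). Power is 0.799 at n = 56 and 0.806 at n = 57. So 57 per arm, 114 in total, is reproduced for **one** comparison. One-sided 2.5% and the two-sided 5% of the analysis section agree numerically and are not part of this point.

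**2. Counting the tests.** One test per outcome and visit, from the outcome sections:

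| Outcome | Visits tested | First-visit (t1) baseline |
|---|---|---|
| KOOS | 5 | yes (implied by Aims) |
| Range of motion | 4 | yes |
| Active leg extension | 3 | yes |
| Tegner score | 5 | yes |
| Isokinetic strength | 2 | no |
| Heel lift | 4 | no |
| Y-balance | 4 | no |
| Jump | 2 | no |
| ACL-RSI | 5 | no |

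Outcomes that can have a change from t1: 5 + 4 + 3 + 5 = 17. All listed: 17 + 2 + 4 + 4 + 2 + 5 = 34. Workability is left out. The KOOS count uses the five time points in Aims, because the timeline figure is not shown.

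**3. Independent tests, all null hypotheses true.** The chance of at least one p < 0.05 is 1 − 0.95^k, and the expected number is 0.05·k.

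| Family | k | Chance of at least one | Expected number |
|---|---|---|---|
| Primary test alone | 1 | 5% | 0.05 |
| KOOS, all visits | 5 | 22.6% | 0.25 |
| Outcome-visits with t1 baseline | 17 | 58.2% | 0.85 |
| All listed outcome-visits | 34 | 82.5% | 1.70 |

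Without the primary test itself, the 17 become 16: 1 − 0.95^16 = 56%. These figures count false positives in either direction. For those favouring the guided programme only, 1 − 0.975^k gives 12%, 35% and 58% for k = 5, 17 and 34.

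**4. Correlated tests.** Repeated measures in the same patients are correlated, and the document gives no correlations. A multivariate normal simulation (200,000 draws) under assumed values gives the chance of at least one false positive:

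| Correlation within / between outcomes | 17 tests | 34 tests |
|---|---|---|
| 0.5 / 0.2 | 48.5% | 71.9% |
| 0.7 / 0.3 | 40.4% | 61.5% |
| 0.7 / 0.5 | 34.8% | 50.1% |
| 0.9 / 0.5 | 27.0% | 41.8% |

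**5. What keeping all tests confirmatory would cost.** With Bonferroni and the normal approximation, power for KOOS at 57 per arm is Φ(d·√(n/2) − z), where z is the two-sided critical value at 0.05/k and d·√(57/2) = 2.85.

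| k | Level per test | KOOS power at 57 per arm | Per arm for 80% |
|---|---|---|---|
| 5 | 0.0100 | 61% | 83 |
| 17 | 0.0029 | 45% | 103 |
| 34 | 0.0015 | 37% | 114 |

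The trial was not sized for the status that the analysis section gives to these tests.

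**The case against.** The strongest reply is that the hierarchy is plain elsewhere. Outcome, time point, contrast and sample size are all fixed for one comparison, and the other measures are called secondary. A reader might infer from the analysis section that the primary hypothesis has been lost. The documents do not support that: Aims, Outcomes and Sample size determination all retain it, and its test has a 5% error rate whatever status the others have.

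A reader might also infer that a false confirmed effect is almost certain. That is not supported either. About 59 independent tests would be needed to reach 95%, and independence is implausible here. The sentence concerns changes from baseline, and five of the nine listed outcomes have no measurement at t1, so its literal reach is about 17 outcome-visits. The section also specifies mixed models without spelling out a test at each visit. One group test per outcome would give 1 − 0.95^9 = 37% for nine outcomes, or 1 − 0.95^4 = 19% for the four with a t1 baseline, if independent. This objection stands as a limit on the size of the problem. Even so, Aims does plan to examine effects at the separate time points.

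Finally, multiplicity procedures are commonly left to a statistical analysis plan, which is not shown, and no passage says that success may be claimed from a secondary result. Both are true. But the point does not rest on a missing procedure. The article states that these analyses are confirmatory. A later plan that restricted this would contradict the published text, so the sentence would still need correcting.

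**Conclusion.** The point holds as a contradiction within the protocol: the analysis section gives confirmatory status to all outcomes and follow-ups at an unadjusted 5%, while the rest of the document defines and sizes the trial for one comparison. The validity of the primary test is not affected. What is affected is which other results may be called confirmed.

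Under the literal 17-test reading, the chance of at least one false confirmed effect is 58% if tests are independent and about 27–49% under the assumed correlations. With 34 tests it is 83%, or about 42–72%. For KOOS alone at five follow-ups it is 23% if independent, and lower with positive correlation. These figures assume that all null hypotheses are true, one test per outcome and visit, KOOS at the five time points in Aims, and correlations of 0.5–0.9 within and 0.2–0.5 between outcomes. Even the lowest figure for the 17 tests is more than five times the nominal 5%.

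**What to change.** In Statistical analysis, replace the sentence on confirmatory status with two statements:

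- The only confirmatory test is the group difference in KOOS sum score change from baseline to the visit 1–7 days before surgery, at two-sided 5%.
- KOOS at later visits and all secondary outcomes are exploratory and are reported as estimates with 95% confidence intervals, without a claim of confirmation.

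If a few secondary claims are wanted, name them and test them in a fixed order after the primary test, each at 5% and only while every earlier test is significant.

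The cost is two sentences. The sample size of 114 and the power of about 80% (80.6% at 57 per arm) stay as they are. The section already plans means with 95% confidence intervals for the main outcome data, so the reporting changes little. The only downside is that secondary results can no longer be called confirmatory.

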### Publication

The results of the study will be published in high-impact peer-reviewed journals to make them available to the orthopaedic and rehabilitation community. In addition, the results of the study will be presented and discussed at scientific conferences.

## Discussion

There is evidence on the relevance of prehabilitation prior to surgical ACL reconstruction to improve neuromuscular and self-assessed knee function, but only with low to moderate quality [12–14]. Further randomised-controlled studies of higher quality and methodology are needed to substantiate the importance of prehabilitation. The conditions of prehabilitation training must be concretized, i.e. the extent, setting, intensity, etc. of the prehabilitation training should be specified and psychological factors (e.g. psychological readiness for return to sport) should be recorded.

The planned study is a single centre and relatively small in size and likely will not be able to define the conditions of prehabilitation completely. Nevertheless, the planned study will help to fill a gap in the evidence regarding the setting of prehabilitation interventions before surgical ACL reconstruction (guided prehabilitation programme vs. self-administered home training).

The last testing in this study is done 180 days after surgery. A longer follow-up would possibly give more details on the potential participants who have still not returned to sports. In recently published studies the follow-up is done up to 3 months after surgery, we extended to 180 days. The follow-up period is therefore relatively long [12].

The conduct of the proposed study presents the following challenges that should be considered:

### Treatment adherence of the participants

In the intervention group, non-adherence to training appointments may reduce the success of prehabilitation training. In the comparator group, there is a risk of lack of motivation to perform home training independently without guidance. In addition, errors in performing the exercises cannot be corrected in the comparator group, since the training is self-administered and without guidance.

### Drop out

In preoperative training programmes that have already been implemented, participant’s compliance was high and the dropout rate was low [39–41]. Nevertheless, there is a risk of dropout in the planned study because the last testing takes place a long time after ACL reconstruction (180 days postoperative). The dropout of the study participation by the patients could distort the results. To keep the drop-out rate low, patients are regularly reminded of their testing dates, and after the testing, they receive their personal test results, which are helpful in assessing the rehabilitation process.

### Time between rupture and reconstruction

The time between injury and surgical treatment is individual and can vary considerably. In previous studies, the time between diagnosis of the ACL injury and surgical treatment was sometimes not reported [12]. To minimise the impact of the training period on outcomes, only participants with the opportunity to complete at least a 3-week training programme are considered eligible. Thus, there is still a risk of a positive influence on outcomes when training for more than 3 weeks.

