## Background

The rupture of the anterior cruciate ligament (ACL) is one of the most common and severe knee injuries [1–3]. Athletes are more endangered to rupture their ACL than inactive individuals [1–3]. In particular in such active patients, the surgical reconstruction of the ACL is the evidence-based rehabilitation and most common treatment after an ACL rupture [4, 5].

Ruptures of the ACL often lead to knee osteoarthritis and secondary instability in the knee joint [6]. Athletes returning to sports after ACL injury have a up to six-fold increased probability of recurrent injury up to 2 years postoperative compared to non-injured athletes [7]. They often perform worse and are characterised by shorter careers than non-injured counterparts [8]. These secondary and follow-up issues often occur after surgical reconstruction despite evidence-based treatments. As a consequence, the rehabilitation process after ACL injuries can still be improved in order to restore the function of the knee and to maintain physical activity and workability. The latter may vice versa lead to a decreased secondary issue or re-injury risk [9]. Clinical practice guidelines for anterior cruciate ligament rehabilitation recommend to include a prehabilitation phase between the injury and the reconstruction [5]. The suggested benefit of preoperative rehabilitation (prehabilitation) is based on the “better-in better-out” strategy. For example, the preoperative maintenance/improvement of conditional and coordinative performance, the improvement of perceived self-efficacy and the reduction of risk factors should enhance the pre- and postoperative functional outcomes and postoperative recovery [10]. The time between injury and reconstruction can vary from a few hours to several months. The later the surgery, the more time there is for preoperative preparation. Most patients are eligible for individually modified preoperative training after the inflammatory phase has ended (about 1 week after injury) [11].

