**Fig. 1 Fig1:**
[figure not shown]
Schedule of enrolment, interventions and assessments (SPIRIT 2013, Standard Protocol Items: Recommendations for Interventional Trials) (t1 = first ambulant presentation in the hospital with confirming the diagnosis, selection of the operator and scheduling the operation, t2 = 1–7 days before surgery, t3 = surgery day, t4 = 30 days post OP, t5 = 60 days post OP, t6 = 90 days t7 = 180 days post OP)

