### Interventions

#### Prehabilitation programme (intervention group)

During the period between injury and surgical reconstruction, the participants of the intervention group perform a structured, criteria-based, guided training at PhysioSport PACE GmbH. The training programme will be adapted to the individual performance level and consists of two training sessions of 60 min per week. In addition, participants receive exercises once a week for self-administered training at home.

The prehabilitation programme is increased progressively and includes the following components [12, 18]Mobilisation of the knee joint, improvement of mobilityImprovement of neuromuscular control, especially of the musculus quadricepsImprovement of postural stability and balanceRestoration or increase of muscle strength (especially knee flexors and extensors, abductors, plantar flexors; local muscle strength endurance training, increase of muscle section, increase of neuromuscular strength).

The choice of exercises is consistent with the exercises in previous studies [12]. In our planned trial, the prehabilitation programme is criteria-based and includes exercises at two levels (level I and level II). The exercise selection and progression are shown in Fig. 2.

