#### Comparator: self-administered home training

In clinical care, the patients usually do not receive any supervised, criteria-based, active therapy prior to surgical treatment. They are most often only asked to exercise on their own. The participants in the comparator group are also asked to exercise on their own and receive a brochure containing six exercises (active knee extension, single leg stands, external hip abduction, hip bridge in the back position, calf lift double legged, squats). These exercises pursue the same goals as the exercises in the guided prehabilitation programme. Participants find information in the brochure about the execution of the exercises and the number of repetitions. The brochure also contains information on the progression of the exercises. As they are all based on usual care exercises, the selection of the exercises and their progression are accompanied by a low risk of injury and follow the same principles as those in the intervention group. The treating physicians at the hospital recommend the participants of the comparator group to perform the exercises three times a week as self-administered, preoperative home training. The participants document independently all self-administered training sessions and other unintended effects. Patients will present this protocol to PhysioSport at preoperative testing. If participants have any questions, they can contact the study management. The self-administered training was chosen as the comparator to investigate the general setting and supervision (one-on-one guidance or self-administered training) of preoperative training after ACL injuries in this trial.

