### Sample — inclusion criteria

Persons aged 16–60 years with unilateral and total primary ACL rupture (confirmed by magnetic resonance imaging) with indication for an arthroscopically assisted, anatomic ACL reconstruction using a hamstring or quadriceps tendon autograft who will be operated at Sana Medical Centre Cologne (inpatient or outpatient) are screened for inclusion. Participants can be included if the length of the period between injury and surgery is at least 3 and no longer than 13 weeks. Only participants who are able to give consent will be included. A parent or guardian must also sign the consent form for non-adult participants (16 or 17 years of age).

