### Study procedure

After ACL injury, anamnesis/testing at the hospital and randomised allocation, participants perform the prehabilitation programme (intervention group: guided prehabilitation programme, comparator group: self-administered home training) (Fig. 3). The training starts at the earliest possible date and lasts until reconstruction (duration at least 3 weeks). For organisational reasons (scheduling of appointments at the hospital) as well as for medical reasons (increased risk of arthrofibrosis during surgery in the inflammatory phase), the period between injury and surgery is at least 3 weeks for most patients at the hospital. The length of the period between injury and surgery as well as all medical decisions (timing of surgery, graft used, etc.) are made independently of the planned study.

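### The named covariates leave out time since injury and available prehabilitation time, although the protocol itself says longer training may affect outcomes; the cost is precision and an unexamined effect modifier, not bias

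*Protocol article*

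**What the plan says.** All places are in the protocol article.

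- **Sample — inclusion criteria:** a patient is eligible if "the length of the period between injury and surgery is at least 3 and no longer than 13 weeks".
- **Study procedure:** "The training starts at the earliest possible date and lasts until reconstruction (duration at least 3 weeks"). The programme has no fixed length. The same section says that the timing of surgery is decided independently of the study.
- **Background:** "Most patients are eligible for individually modified preoperative training after the inflammatory phase has ended (about 1 week after injury").
- **Interventions:** the guided programme "consists of two training sessions of 60 min per week". Comparator patients are advised to "perform the exercises three times a week as self-administered, preoperative home training".
- **Outcomes:** the primary time point, t2, is 1–7 days before reconstruction, so it moves with the surgery date. Under Aims, the hypothesis concerns the change in KOOS sum score from baseline to pre-reconstruction.
- **Fig. 1 legend:** t1 is the first hospital presentation and includes "selection of the operator and scheduling the operation".
- **Discussion, Time between rupture and reconstruction:** the interval is said to vary considerably, a 3-week minimum is offered to limit its impact, and the text then concedes "Thus, there is still a risk of a positive influence on outcomes when training for more than 3 weeks".
- **Statistical analysis:** in the main model, "the influence on the treatment effect by clinically important confounders and effect modifiers age, gender, and activity level will be calculated". No interval variable appears in that list.
- **Randomisation procedure:** 1:1 in permuted blocks of random size. No stratification factor is stated.

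**The concern.** Baseline is tied to the first hospital visit and the primary time point to surgery. The time between the two KOOS measurements therefore differs widely between patients, and with it both the training received and the natural recovery. The Discussion recognises that training time may move the outcome. Its only safeguard is a minimum, which does nothing about differences above three weeks, and the covariates named for the confirmatory model do not pick the matter up.

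Two things are at stake. First, variation in KOOS change that pre-randomisation dates could explain stays in the residual. Second, the trial reports one effect averaged over very different training times, with no planned look at whether guidance helps more when there is more time to train. The Discussion says that the extent of prehabilitation needs to be specified. A null result would leave open whether guidance does not help or whether many patients had too little time for it to do so.

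The floor itself is also stated in two ways. The inclusion criteria count three weeks from injury to surgery. Study procedure and the Discussion count three weeks of training, which starts later than the injury.

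**Working it through.** **1. The plan's own sample size.** Inputs from Sample size determination: difference 8 (lower end of the 8–10 range), SD 15, one-sided alpha 2.5%, power 80%.

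d = 8/15 = 0.533. A two-sample t-test (noncentral t) gives 79.9% power at 56 per arm and 80.6% at 57. The stated 57 per arm, 114 in total, is reproduced.

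**2. Spread of the intervals.**
- Injury to surgery: 13/3 = 4.3-fold.
- Training time: at least 3 weeks. If training starts about 1 week after injury, the maximum is about 13 − 1 = 12 weeks, so 12/3 = 4-fold.
- Guided sessions at two per week: 2 × 3 = 6 to 2 × 12 = 24.

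**3. Variance explained by training time.** Assumptions, because the document gives neither: training time is uniform over 3 to 12 weeks, and natural KOOS recovery is linear at b points per week. SD 15 is taken to include this variation already.

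SD of training time = 9/√12 = 2.60 weeks. Share of variance = (b × 2.60)²/15². Residual SD = 15 × √(1 − share). Power is for 57 per arm and a difference of 8.

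| b (points/week) | SD from time (points) | Share of variance | Residual SD | Power after adjustment |
|---|---|---|---|---|
| no adjustment | – | – | 15.00 | 80.6% |
| 0.5 | 1.30 | 0.75% | 14.94 | 80.9% |
| 1 | 2.60 | 3.0% | 14.77 | 81.8% |
| 2 | 5.20 | 12.0% | 14.07 | 85.3% |

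Losing two degrees of freedom changes none of these power figures at the precision shown.

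**4. Is the unadjusted comparison biased?** This was checked with 20,000 simulated trials per scenario, 57 per arm, with the interval uniform over 3–13 weeks and independent of arm, and slopes of 0, 1, 2 and 3 points per week. There was no adjustment for the interval.
- No treatment effect: mean difference 0.0, two-sided rejection rate 0.048 to 0.052.
- Constant effect of 8: mean estimate 7.97 to 8.03, power about 0.80.
- Effect growing by 1 point per week trained (mean 8): mean estimate 7.97 to 8.03, power 0.76 to 0.80.

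The unadjusted contrast estimates the average effect and holds its type I error.

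**5. Chance imbalance.** The standard error of the difference in mean training time between arms is 2.60 × √(2/57) = 0.49 weeks. That is 0.24, 0.49 or 0.97 KOOS points at the three slopes. It is already part of the total standard error, 15 × √(2/57) = 2.81 points.

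**6. The three-week floor.** A patient operated on 3 weeks after injury meets the inclusion criterion. If training starts about 1 week after injury, that patient has about 3 − 1 = 2 weeks of training, less than the 3 weeks that Study procedure and the Discussion require.

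**The case against.** A reader might infer that the primary estimate confuses training dose, natural recovery and treatment effect. That describes the change within one arm. The hypothesis and the model compare randomised groups, and surgery timing is stated to be independent of the study, so interval and recovery are balanced in expectation. The simulation agrees. Chance imbalance is ordinary sampling error. This part of the objection stands in full.

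Nor does the omission break the power calculation. If SD 15 already contains the interval variation, 114 patients meet the 80% target without adjustment, and the covariate only adds to it. The gain rests on an assumed slope and is negligible at 0.5 points per week. This also stands.

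Other stronger readings fail too. Baseline cannot fall anywhere in the 3–13 week window, because at least three weeks of training must follow. Twenty-six guided sessions (2 × 13) would need training from the day of injury. The range is also bounded above, at 13 weeks.

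Averaging over the waits that occur in practice is a legitimate estimand. Session logs and compliance reporting in both arms allow some exploratory description of dose. However, sessions completed arise after randomisation and cannot replace a pre-randomisation measure of available time.

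It may be said that covariates belong in an analysis plan that is not shown. Here the article does not defer the choice: it names the covariates for an analysis it calls confirmatory and leaves out the influence its own Discussion raises. That the scheduled date exists before allocation is inferred from scheduling at t1 and the eligibility rule. No section says so outright, and the fix must make it explicit.

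**Conclusion.** The point holds as a matter of precision and interpretation. Time since injury and available prehabilitation time vary about fourfold and the protocol recognises that training time may matter, but neither is among the named covariates. The randomised comparison remains unbiased with correct type I error, and the unadjusted design meets its 80% target at 80.6%.

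Adjustment would bring about 0.3, 1.2 or 4.7 percentage points of power at 0.5, 1 or 2 KOOS points per week. These figures assume a uniform 3 to 12 weeks of training and a linear slope, neither of which the document gives. The other loss is that a modifier raised by the protocol goes unexamined.

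Bias would require surgery timing to differ by arm. The document says timing is independent of the study, so bias cannot be asserted. Because the hospital physician sees the allocation, reporting the interval by arm is a reasonable check. The two versions of the three-week floor are a separate inconsistency that needs reconciling. Overall this is a low-severity but nearly free improvement.

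**What to change.** 1. **Statistical analysis:** add two fixed-effect covariates, days from injury to t1 and days from t1 to the surgery date scheduled at t1. Require both dates to be recorded before the envelope is opened. Use the scheduled date. Actual weeks or sessions completed arise after randomisation and should not be adjusted for in the main analysis.
2. **Same section:** list group by scheduled duration as an exploratory effect modifier only. With 57 per arm it will be imprecise.
3. **Results reporting:** give the scheduled and actual injury-to-surgery intervals by arm.
4. **Discussion, Time between rupture and reconstruction:** say that the three-week minimum sets a floor and does not control for training length.
5. **Inclusion criteria, Study procedure and Discussion:** reconcile three weeks from injury to surgery with three weeks of training.

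Cost: two dates that the eligibility rule already calls for, two degrees of freedom, a few sentences, and the discipline of recording the scheduled date before allocation. No extra patients or visits are needed.
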